### Inclusive criteria

2.4

The inclusion criteria will be as follows: clinical diagnosis of first-episode unilateral cerebral hemisphere infarction or cerebral hemorrhage, with confirmation using CT or MRI; meeting the diagnostic criteria for dysphagia; showing abnormal expressions of the oral and pharynx stages upon VFSS evaluation; having stroke and dysphagia duration within 3 months; being conscious with stable vital signs and a mini-mental state examination score of ≥ 21; age 45 to 75 years; and having provided informed consent.

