### The drop out of cases and disposal

2.6

The criteria for drop-out cases will be as follows: voluntary withdrawal from the study; being unsuitable for further assessment due to severe adverse reactions, severe complications, or condition deterioration; poor compliance that impedes the provision of consent for study participation; or incomplete treatment evaluation without rule compliance and with insufficient observation data.

Regarding the disposal of drop-out cases, researchers should adopt home visits, phone, letters, etc to communicate with the participants, record the last treatment time, and extensively perform evaluation. After obtaining the drop-out reasons, they will be added to the case report form. All observation data from drop-out cases will be collected for analysis by the project teams. The researcher should record details regarding drop-out information and enroll more than one treatment course to be included in the efficient statistics.

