### The discontinuity and management of cases

2.7

Participants shall be discontinued during the trials in case of occurrence of serious adverse reactions, severe complications, or condition deterioration. Moreover, the clinical trials will be suspended according to the doctors’ judgment, if required.

Regarding management of discontinued cases, the doctor will take some relevant clinical disposals after discontinuation. Subsequently, the doctor will perform a detailed investigation of the reasons and retain the obtained observation data. The last obtained result will be used as the final result and included in the analysis of efficacy and adverse reactions.

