### Sample size calculation

2.16

Referring to Liu Zhishun's “clinical study on acupuncture treatment of chronic moderate and severe dysphagia in stroke,” the effective rate of traditional rehabilitation is 80%, the estimated effective rate is 93.3%. According to the preset parameters, the effectiveness of the two groups were calculated with PASS 8.0 software, and 97 samples were needed for each group. At the same time, abscission and elimination were considered. The abscission rate was 30% and each group needed 126 samples. Therefore, 252 subjects were expected to be included in this study.

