### Statistical analysis

2.17

A third-party medical statistics professional (Guangdong Provincial Hospital of Traditional Chinese Medicine) will perform statistical analysis. After the subject research plan and case report form are reviewed by experts, a third party will formulate a statistical analysis plan and determine the statistical software to use.

1.Full Analysis Data Set (FAS): A total of 252 random numbers were designed in this study to exclude subjects in a minimum and reasonable manner according to the principle of intentionality analysis. This data set includes all subjects receiving treatment. Missing data for key indicators are carried forward to the closest observation (LOCF).2.Per-Protocol Data Set: those who have good compliance (who have received at least 2/3 or more of the courses of treatment), whose main indicators of observation are not missing, who have basically not violated the Protocol, and who meet the inclusion criteria without any exclusion indicator constitute the current PP population. Missing data in this data set is not carried forward, but is treated as missing data.

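### Last observation carried forward is the only stated missing-data rule for the full analysis set; in patients still recovering from stroke it can bias the comparison by an amount and in a direction the protocol does not fix

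*Protocol article*

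**What the plan says.** Section 2.17 defines the full analysis set as all treated subjects and gives it one rule for gaps: "Missing data for key indicators are carried forward to the closest observation (LOCF"). The per-protocol set is not imputed and requires the main indicators to be present.

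Section 2.7 says when treatment ends early: "Participants shall be discontinued during the trials in case of occurrence of serious adverse reactions, severe complications, or condition deterioration". For those patients, "The last obtained result will be used as the final result and included in the analysis of efficacy and adverse reactions".

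Section 2.6 lists among the drop-out criteria "being unsuitable for further assessment due to severe adverse reactions, severe complications, or condition deterioration". It also asks staff to contact drop-outs, evaluate them and collect all their data. Section 2.8 lists withdrawals and patients with insufficient data as excluded cases.

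Eligibility (2.4) requires "having stroke and dysphagia duration within 3 months". Section 2.10.1 names SSA and VFSS as primary. Table 1 schedules VFSS at baseline and week 2 only, and SSA at baseline, week 1, week 2 and 1 month after the intervention ends.

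On planned loss, 2.16 says "At the same time, abscission and elimination were considered", and then "The abscission rate was 30% and each group needed 126 samples".

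**The concern.** Carrying a score forward assumes that it would have stayed where it was. The trial's own planning contradicts this: 2.16 expects 80% of control patients to become effective, so change is expected in both arms.

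The rule acts differently on the two primary outcomes. For VFSS the only earlier value is baseline, so a carried value means zero change. For SSA the carried value may be baseline or week 1. When the reason for loss is a complication or deterioration, that score predates the event.

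Three things are at stake. If loss differs between the arms, the rule can turn a difference in loss into a difference in outcome; differing loss is plausible because patients know their treatment (2.15). If loss is equal and the treatment works, the rule can shrink the effect. In both cases the filled-in values are analysed as if observed, so their uncertainty is left out of the standard error.

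**Working it through.** **The plan's own figure.** Inputs from 2.16 are effective rates of 80% and 93.3%, 97 per group, and 126 after allowance for loss. Alpha and power are not stated; I assume 5% two-sided and 80%. The arcsine formula gives h = 2·asin(√0.933) − 2·asin(√0.80) = 0.4036 and n = 2·((1.960 + 0.842)/h)² = 96.3, i.e. 97. Then 97 × 1.3 = 126.1, which is the stated 126. The figures reproduce. At 126 per arm, loss can reach (126 − 97)/126 = 23% before fewer than 97 remain.

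**Effect of carrying forward.** Let d be the loss in an arm, p the true final effective rate (taken to be the same in lost and retained patients), and q the share of lost patients already effective at their last visit. The expected analysed rate is

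(1 − d)·p + d·q.

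The document gives neither d by arm nor q, so both are assumptions. For VFSS, q = 0 is the natural value because baseline is carried. For SSA, q can exceed 0 because of the week-1 visit. Rejection rates are exact enumerations of the uncorrected chi-square test, two-sided 5%, 126 per arm.

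*No true effect (p = 0.80 in both arms):*

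| Loss | q | Analysed rates | Difference | Rejected |
|---|---|---|---|---|
| 20% vs 40% | 0 | 64% vs 48% | 16 points | 73% |
| 20% vs 40% | 0.2 | 68% vs 56% | 12 points | 50% |
| 20% vs 40% | 0.4 | 72% vs 64% | 8 points | 28% |
| 20% vs 40% | 0.6 | 76% vs 72% | 4 points | 11% |
| 25% vs 35% | 0 | 60% vs 52% | 8 points | 25% |
| 25% vs 35% | 0.4 | 70% vs 66% | 4 points | 11% |
| 25% vs 35% | 0.6 | 75% vs 73% | 2 points | 7% |
| 30% vs 30% | any, same in both arms | equal | 0 | 5% |

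First row: 0.8 × 0.8 = 0.64 and 0.6 × 0.8 = 0.48.

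*Planned effect, equal 30% loss:*
- q = 0: 0.7 × 0.933 = 65.3% vs 0.7 × 0.80 = 56.0%, a difference of 9.3 points and power of about 32%.
- q at half the final rate (0.4665 and 0.40): 0.653 + 0.3 × 0.4665 = 79.3% vs 0.56 + 0.3 × 0.40 = 68.0%, a difference of 11.3 points and power of about 53%.

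The planned difference is 13.3 points.

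**Deterioration.** If a share f of lost patients truly deteriorated, and a share q of those were effective at the last visit, the arm's rate is overstated by d·f·q. With d = 0.30, f = 0.5 and q = 0.4 that is 6 points. The range is 1.5 points (f = 0.25, q = 0.2) to 18 points (f = 1, q = 0.6). This applies to SSA; on VFSS the carried baseline shows no improvement.

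**Who is carried forward.** Section 2.17 carries forward missing key indicators in all treated subjects, and 2.7 does so for discontinued cases. Section 2.8 excludes withdrawals and patients with insufficient data. Section 2.6 wants all drop-out data analysed, yet appears to admit to the efficacy statistics only those with more than one treatment course. These cannot all be applied to the same patient.

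**The case against.** Several stronger readings are tempting, and the documents do not support them.

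- *The result will be biased, or biased towards acupuncture.* With equal loss, equal q and no true effect, the difference is unbiased. With other inputs the rule can shrink, inflate or reverse the difference.
- *The false-positive rate will be 73%, or power 32%.* Both need q = 0, and the first also needs an assumed 20% vs 40% split. They are upper-end illustrations.
- *30% of data will be missing.* That allowance covers drop-out and elimination together. Eliminated cases under 2.8, such as wrong-group patients, may have complete data.
- *Every deteriorating patient is credited with success.* On VFSS a carried baseline is no improvement. The crediting problem concerns SSA.
- *Every drop-out receives the baseline VFSS.* Sections 2.6 and 2.8 may remove some of them altogether, and the evaluations that 2.6 requests could fill some gaps.

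It can also be said that 2.17 defers detail to a statistical analysis plan that is not shown, so sensitivity analyses cannot be assumed absent. That is fair, but carrying forward is a choice the protocol makes, not a detail left open. The per-protocol set is no check on it, since it leaves out the patients whose main indicators are missing.

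**Conclusion.** The point holds as a badly fixed analysis choice. The sole stated rule for the full analysis set assumes no change after loss, in patients expected to change, and some of the listed reasons for loss are themselves linked to outcome. How far this moves the primary comparison cannot be determined from the protocol. Under the assumptions shown, false positives run from the nominal 5% (equal loss) to about 73%, and power under equal 30% loss is about 32% to 53%. I am confident that the rule is unsuitable as the main method, and not confident about any single figure for the bias. The contradiction over who is carried forward stands on the text alone and needs no numerical assumption.

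**What to change.** 1. In 2.17, replace carrying forward as the main full-analysis-set method. For SSA, use a mixed model for repeated measures on the visits already scheduled. For VFSS, use multiple imputation by arm, with baseline VFSS and week-1 SSA as predictors.
2. Both methods assume data missing at random, while some of the loss here depends on outcome. Add a missing-not-at-random sensitivity analysis, for example delta-adjusted or tipping-point. Carrying forward may stay as a further sensitivity analysis only.
3. For any effective-rate analysis, state the estimand for patients stopped for adverse reactions, complications or deterioration. If they count as not effective, declare this as a composite outcome. Otherwise it is simply the q = 0 rule for those patients, with the same sensitivity to unequal loss.
4. Analyse the evaluations that 2.6 already asks staff to obtain after drop-out.
5. Reconcile 2.6, 2.7, 2.8 and 2.17 on whether such patients are excluded, carried forward or analysed as observed.

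The cost is revised wording in the protocol and analysis plan and modest extra analysis work. No new visits are needed beyond those in Table 1 and the contacts that 2.6 already requires.

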## Discussion

3

Dysphagia refers to swallowing dysfunction.^[11]^ Clinical patients are commonly in the oral, pharyngeal, or both stages. The mouth stage is the chewing food process to form a bolus, with the tongue moving the bolus back and forth before entering the pharynx. Dysfunction involves weakness of the facial muscles, including the chewing, labial, and tongue muscles, which impedes food bolus formation and smooth delivery to the pharynx. The pharyngeal stage refers to the process of the food bolus entering the oropharynx into the esophagus. This stage involves abnormal pharyngeal muscle and laryngeal function, which often causes aspiration, pharynx retention, and hoarseness.^[12]^

The SSA is divided into three parts: clinical examination, observation of patients swallowing 5 mL of water, and observation of patients swallowing 60 mL of water. It has a total score of 46, with the lowest possible score being 17. A higher cumulative score of each item indicates worse swallowing function. Some studies have reported that SSA is more feasible and suitable for evaluating dysphagia.^[13]^ The SSA includes 10 items divided into four levels: independent, less dependent, moderately dependent, and completely dependent. The VFSS allows dynamic assessment of the swallowing function of the mouth, pharynx, and upper esophagus using TV fluoroscopy. The VFSS is considered the “gold standard” for evaluating swallowing function. It is widely used for the comprehensive evaluation of the patients’ oral, pharyngeal, and esophageal swallowing conditions.^[14]^ The sEMG allows evaluation of the physiological process of swallowing. It is a simple and reliable screening that allows preliminary identification of dysphagia and has advantages of accuracy, rapidity, and non-invasiveness.^[15]^ fMRI is a safe, non-invasive, and non-radiation imaging method with high temporal and spatial resolution. Anatomical and functional images can be simultaneously obtained in a single imaging session.^[16]^

Acupuncture is commonly applied in stroke rehabilitation; however, there remains no high-quality evidence regarding acupuncture efficacy. There are numerous acupuncture types, including scalp, body, nape, and latch acupunctures, as well as awn needles, which are all used for the treatment of post-stroke swallowing dysfunction. Neck acupuncture can directly act on the throat, as well as stimulate hypoglossal and recurrent laryngeal nerves. Fengchi and other acupoints can stimulate the occipital artery, occipital vein, vertebral artery, and vertebral vein, as well as promote blood circulation.^[17]^ This large-scale, multicenter, randomized controlled trial will employ neck acupuncture to assess its treatment effect on post-stroke swallowing dysfunction.
